#### Aim 2: Analyses

Specific aim 2 analyses will further probe the eSCCIP/eSCCIP-SP user experience, intervention effects, and boundary conditions. First, descriptive summaries and data visualizations will be used to explore user engagement variables, such as the number of cores completed. Next, potential risk and protective factors will be examined by introducing interaction effects to the models previously described for specific aim 1, including all primary and secondary end points. Interaction terms will be formed between intervention assignment and each potential moderator variable, tested in separate models under the Benjamini-Hochberg control method. Follow-up inferential and graphical procedures will be used to interpret significant interaction effects [57]. Variables selected as potential moderators are participant characteristics guided by the Behavior Change Model for Internet Interventions (eg, race, gender, and socioeconomic status) and family risk variables guided by the Pediatric Preventative Health Model (eg, COVID-19 Exposure and Family Impact Scale score, PAT baseline score). Of primary importance is the potential moderating effect of intervention language, which will similarly be tested. Additional exploratory analyses will be carried out to answer key auxiliary questions and maximize the use of the data collected. First, we will examine any possible persisting effects of eSCCIP/eSCCIP-SP at the 3-month follow-up time point, based on longitudinal analysis models designed for randomized pretest-posttest-follow-up designs [58]. Similarly, we will also explore whether treatment effects differed between parents and caregivers of children with cancer from families with 1 or 2 participating caregivers, as well as examine trends in data provided by nonprimary participating caregivers.

#### Aim 3: Analyses

Qualitative interviews will be coded and analyzed using the CFIR framework, a widely used implementation science framework. An initial codebook will be generated using different domains of the CFIR framework, focusing on the constructs within each domain that are most related to the implementation of eSCCIP/eSCCIP-SP (eg, adaptability, cost, patient needs and resources, and self-efficacy). Discrepancies will be identified and resolved by consensus among the investigators. To strengthen the rigor of the analysis, a primary and secondary coder will be assigned as the analysis continues with the secondary coder checking the coding of the primary coder as well as completing a summary of data on each category within that case (group) and across all cases (groups). The case summaries and samples of the coding process will be reviewed in regular meetings of the study team. Through this content analysis process, codes will be transformed into categories and categories into themes according to national standards that identify and refine strategies for the implementation of the intervention. Themes that result from this process will be translated into implementation and sustainability strategies organized around the 5 major domains of the CFIR framework. We will explore intervention characteristics, inner and outer settings, characteristics of individuals, and the implementation process.

The incremental (ie, beyond the cost of an education control website) costs and cost-savings analysis will follow best practices. We will estimate incremental costs associated with eSCCIP/eSCCIP-SP treatment, costs per participant, and marginal costs per unit of acute distress reduction. All costs will be estimated and evaluated in constant dollars using the appropriate index for price adjustment. Those resources that rise at the rate of general inflation will be corrected for inflation with the consumer price index, while medical costs will be adjusted with the medical component of the consumer price index. Due to the efficacy trial nature of this project, we will conduct a partial economic evaluation to document the cost information of the eSCCIP/eSCCIP-SP and estimate a preliminary cost-effectiveness regarding the primary outcome (ie, acute distress reduction). We will evaluate the intervention costs from health care provider perspective; therefore, the nonresearch-related cost/resource will be those health care provider–related ones, which will include intervention labor costs for hourly wages including fringe benefits of delivery staff for a different component of the program (ie, website regular maintenance staff, and telehealth guide). During all phases of development and implementation, we will document what was performed, by whom, the length of execution, and the use of any nonhuman resources. Cost collection instruments will be modified based on the eSCCIP guide/research team templates and behavioral intervention templates. Care will be taken to accurately separate research-based costs (eg, costs of follow-up assessments) from actual worksite program implementation costs. We will estimate separate costs for eSCCIP and eSCCIP-SP to provide the information needed to compare differences and provide evidence for predicting costs based on patients’ ethnicity distribution. To capture cost savings from a health care provider’s perspective, we will use electronic patient record to track control group patients’ related health care service usage, which provides the relevant information to estimate potential cost savings patients in the treatment group could have used if there is no eSCCIP/eSCCIP-SP. A full-scale cost-effectiveness analysis will be out of the scope of this efficacy study. We will calculate incremental cost-effectiveness ratios and will use bootstrapping methods to account for the uncertainty around the incremental cost-effectiveness ratios but recognize that the limited scope of this study: only collecting partial information on program costs, especially on implementation costs [59]. We will calculate net benefits, benefit-cost ratio, and return on investment (return on investment=net benefits/costs×100). Bootstrapping will be used for CIs construction around those measures. Generalized linear models will be applied to estimate the relationship between program incremental costs and the characteristics of participants, providers, and programs. Appropriate link function and distribution family will be chosen to fit the data. A 2-part model will be used to examine and handle sample selection and nonrandom attrition.

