### Study Procedure

Potential participants will be screened for eligibility using a brief, web-based screening questionnaire that is accessible by direct contact with a member of the study team or through the study interest website. Once screened, an RC will confirm eligibility and instruct participants about the consent process. Web-based consent procedures will be conducted via DocuSign or a similar secure software. Once web-based consent is complete, participants will receive a unique username and password to log onto their randomized condition (eSCCIP/eSCCIP-SP or education control). Study questionnaires will be completed through this web platform. As there are no required components of the education control, automated or RC-directed text and email reminders to use the program will not be required for individuals randomized to the education control.

After completion of the initial web-based assessment battery, participants in the intervention condition will schedule their initial telehealth session using an automated scheduling tool available through the platform hosting eSCCIP/eSCCIP-SP. Participants will be notified that the overview core and core 1 need to be completed prior to the telehealth session. Automated reminders will be sent at regular intervals to encourage participation in study cores. Manual follow-up by RCs will also be initiated in cores that are not completed. Cores will automatically unlock at 1-week intervals, and telehealth sessions will be scheduled directly with the participant. A total intervention completion window of 4-6 weeks will be anticipated by the study team for each participant, building in some additional time for start-up and potential scheduling delays. A similar process has been successfully implemented in eSCCIP pilot studies [24,30]. Because eSCCIP/eSCCIP-SP cores and the education control website are delivered digitally, all parents and caregivers of children with cancer will have convenient access to their respective condition’s content anywhere the internet is available.

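### The Aim 3 list of costed delivery staff leaves out research coordinators, who follow up incomplete cores; applied as written, it would understate the intervention's cost

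*Protocol article*

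**What the plan says.** All references are to the protocol article.

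- **Outputs.** Aim 3: Analyses commits to this: "We will estimate incremental costs associated with eSCCIP/eSCCIP-SP treatment, costs per participant, and marginal costs per unit of acute distress reduction". It adds cost-effectiveness ratios, net benefits, a benefit-cost ratio and return on investment, and separate costs for eSCCIP and eSCCIP-SP.
- **Perspective and labor.** "We will evaluate the intervention costs from health care provider perspective". The labor is wages and fringe benefits of "delivery staff for a different component of the program (ie, website regular maintenance staff, and telehealth guide".
- **Research boundary.** "Care will be taken to accurately separate research-based costs (eg, costs of follow-up assessments) from actual worksite program implementation costs".
- **Recording.** Over development and implementation, "we will document what was performed, by whom, the length of execution, and the use of any nonhuman resources".
- **Stated limit.** The evaluation is called partial, "only collecting partial information on program costs, especially on implementation costs".
- **Coordinator work.** Study Procedure says of the intervention arm: "Manual follow-up by RCs will also be initiated in cores that are not completed". Of the other arm it says that "automated or RC-directed text and email reminders to use the program will not be required for individuals randomized to the education control", because the control has no required components.

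**The concern.** Coordinator contact about an unfinished core is aimed at getting participants through the intervention's own content. It is not aimed at completing questionnaires. If it works, it raises exposure to the intervention, and the trial's effect estimate is obtained with that support in place. The labor list opens with ie, which specifies, whereas the same section uses eg when it gives an example. Coordinators are not on the list.

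A provider reading the cost results would then see an effect achieved with human adherence support, set against a labor cost that leaves part of that support out. The planned bootstrap intervals reflect sampling uncertainty and cannot restore an item that was never costed.

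**Working it through.** The plan states no cost, wage, session length or coordinator time, so there is no figure to reproduce. The check is a comparison of text, then the direction of the error, then an illustration on assumed inputs.

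**1. Text side by side**

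| Question | Where | What it says |
|---|---|---|
| Who is costed as delivery labor? | Aim 3: Analyses | Website maintenance staff and the guide |
| Who works to get cores completed? | Study Procedure | Coordinators, by hand, besides automated reminders |
| Is this needed in control? | Study Procedure | Not required |
| What is a research cost? | Aim 3: Analyses | Only example: follow-up assessments |
| Can a coordinator be part of delivery? | Randomization | Only coordinators outside delivery are kept from allocation, which implies that some may be inside it |

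A coordinator who chases an unfinished eSCCIP core necessarily knows the allocation. The Randomization wording therefore places that coordinator with delivery, and the staff list does not cover the role.

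**2. Direction**

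Let C be the counted incremental cost, o > 0 the omitted coordinator cost, E the incremental effect and B the savings.

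- Incremental cost: C is reported in place of C + o, so it is too low. Cost per participant falls in the same way.
- Cost per unit of distress reduction: C/E < (C + o)/E when E > 0.
- Net benefit: B − C > B − C − o, so it is too high.
- Return on investment: (B − C)/C = B/C − 1, which falls as C rises when B > 0, so it is too high.

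**3. Illustrative size**

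Only the 3 guide sessions come from the documents (Study Platform). The other inputs are assumptions:

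- guide time h = 0.75 to 1.5 hours per session;
- maintenance m = 0 to 0.5 guide-hour equivalents per participant;
- coordinator-to-guide wage ratio w = 0.4 to 0.6;
- coordinator follow-up r hours per participant.

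Proportional increase in counted labor = r·w / (3h + m).

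The smallest increase uses h = 1.5, m = 0.5, w = 0.4, so the denominator is 3 × 1.5 + 0.5 = 5.0. The largest uses h = 0.75, m = 0, w = 0.6, so the denominator is 3 × 0.75 = 2.25.

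| r (hours) | Smallest | Largest |
|---|---|---|
| 0 | 0% | 0% |
| 0.5 | 0.2/5.0 = 4% | 0.3/2.25 = 13% |
| 1 | 0.4/5.0 = 8% | 0.6/2.25 = 27% |
| 2 | 0.8/5.0 = 16% | 1.2/2.25 = 53% |

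For a fixed positive effect, labor cost per unit of distress reduction rises by the same proportion. The table shows how the answer depends on r. It is not an estimate for this trial.

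**The case against.** The strongest reply is that the omission is inferred. The protocol never classes coordinator follow-up as research or as delivery. The activity log covers all work by person and duration, the cost instruments draw partly on research team templates, and the labor items are ones that provider costs will include, which leaves room for other kinds of cost. The evaluation is declared partial, preliminary and exploratory. Treating the time as research is also arguable: Study Platform describes a program designed to run fully automatically, and Limitations mentions reminders in the context of retention. An article may also leave item-level costing rules to a fuller document.

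Much of this stands, and it limits the claim to what happens if the list is applied as written. It does not remove the point. The log records time but does not place it in the costed labor. The general caveat names neither this item nor the direction of its bias. The article does not stay silent on who is costed: it specifies the staff, and the list does not fit its own description of delivery.

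A reader might infer more than the documents support:

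- **That costs are certainly understated.** This depends on the list being applied literally and on follow-up taking appreciable time.
- **That the omission has a known percentage.** Every time and wage is assumed.
- **That the eSCCIP versus eSCCIP-SP cost comparison is distorted.** Nothing indicates that follow-up differs by language.
- **That coordinator scheduling is omitted too.** Study Procedure describes an automated tool for the first session and no coordinator scheduling for the later ones.
- **That control participants get no reminders.** The text says they are not required, which is not a prohibition.

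**Conclusion.** The concern holds in conditional form. The staff list and the described delivery do not match. Applied as written, the list leaves out an intervention-arm labor cost whose benefit remains in the effect, so the cost measures would err in the intervention's favor. For cost per unit of distress reduction this also requires a positive effect, and for return on investment positive savings. The size cannot be determined from the documents: it is zero if no follow-up is needed, and about 4% to 53% of counted labor for 0.5 to 2 coordinator hours per participant under the assumptions above. The consequence is confined to the exploratory cost results; the primary and secondary efficacy analyses do not use them. The correction is worth making because it is cheap and because time that was not tagged when logged is hard to split afterwards.

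**What to change.** Add one costing rule to Aim 3:

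1. Coordinator time spent on core-completion follow-up is intervention delivery labor, costed at wages plus fringe benefits like the other delivery staff.
2. In the activity log, tag this time separately from recruitment, consent and assessment follow-up, which remain research cost.
3. Report incremental cost, cost per participant, the cost-effectiveness ratio, net benefit, benefit-cost ratio and return on investment with and without this item, separately for eSCCIP and eSCCIP-SP.

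Reporting both ways lets a reader who regards the time as research see that version too. The log is already planned, so the cost is minor extra tagging and a slightly less favorable cost figure.

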### Randomization

Randomization will be conducted at the family level according to a 1:1 ratio between groups, in permuted blocks of 6, stratified by site and language preference. The study data analyst at site A will use an Excel (Microsoft Corp) spreadsheet with a randomization scheme created by the study biostatistician to randomize families. This spreadsheet will be inaccessible to any members of the study team aside from the data analyst. It is not possible for study telehealth guides to be blinded to the intervention condition because of the in-person contact required for eSCCIP/eSCCIP-SP; however, study investigators and research coordinators (RCs) not involved in intervention delivery will not have access to random assignment information. After randomization, participants will be instructed on the procedures within their assigned group. All outcome measures will be completed directly on the web by study participants, further reducing the risk of bias.

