### Study Outcomes

Data will be collected at 3 time points: prior to beginning the intervention (T1), postintervention (after 6 weeks; T2), and at 3-month follow-up (3 months after baseline; T3). Outcome measures include the Psychosocial Assessment Tool (PAT) [39,40], the Multidimensional Scale of Perceived Social Support [41], the Kessler Psychological Distress Scale (K-6) [42,43], the COVID-19 Exposure and Family Impact Scale [44], the Coping Self-Efficacy Scale [45], the Cognitive Emotion Regulation Questionnaire [46], Distress Thermometer [47], the Patient-Reported Outcomes Measurement Information System Short Form (PROMIS Short Form v1.0—Anxiety-8a) [48], the posttraumatic stress disorder checklist [49], as data on previous psychosocial service usage. Individuals randomly assigned to the intervention condition will also complete a questionnaire at T3 measuring satisfaction and acceptability with the intervention, which has been used in all prior eSCCIP studies. Measure description and schedule for data acquisition are provided in Table 1.

**Table 1 table1:** Outcome measures and assessment timing schedule.

Domain or measure	Description	T1^a^	T2^b^	T3^c^
Chart review	Review of patient medical record			
Demographic variables of parents and caregivers of children with cancer	Demographic variables of enrolled parents and caregivers of children with cancer	✓		
Previous psychosocial service usage	Questionnaire to measure contact and work with social work, psychology, psychiatry, pastoral care, community, and hospital-based services for all members of the family	✓	✓	✓
PAT^d^	Brief parent report screener of psychosocial risk [39,40]	✓		
MSPSS^e^	Questionnaire to measure perceived social support from family, friends, and significant other [41]	✓	✓	✓
K-6^f^	Questionnaire to measure acute distress [42,43]	✓	✓	✓
CEFIS^g^	Questionnaire to measure the extent to which a family has experienced or been “exposed” to COVID-19–related potentially traumatic events (eg, economic changes, illness in family) and the impact of these events on the family’s functioning and well-being [44]	✓	✓	✓
CSES^h^	Questionnaire to measure the perceived ability to cope effectively with challenging situations across 3 domains (use problem-focused coping, stop unpleasant emotions and thoughts, and get support from friends and family) [45]	✓	✓	✓

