Finally, it is also important to acknowledge that care at study sites includes access to psychosocial support; however, the use of these services is likely to be equivalent across intervention and control group participants, and no participant in either condition will be discouraged from accessing any available psychosocial support. While usual care may include work with a licensed psychologist, novel aspects of eSCCIP are unique to the intervention and not a component of routine care. We will also collect information on mental and psychosocial health services used by all participants during the study period to understand the context in which eSCCIP/eSCCIP-SP was received and control for other psychosocial services in analyses if indicated.

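### Cost savings are to be estimated from record-tracked service use in the control arm, with no stated tracking, costing or subtraction of intervention-arm use

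*Protocol article*

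**What the plan says.** In the Protocol article, Aim 3: Analyses, the economic work is framed as incremental to the education control website, taken from the health care provider's perspective, and partial in scope. For savings, the text says "we will use electronic patient record to track control group" patients' related service use. The stated purpose is to "estimate potential cost savings patients in the treatment group could have used if there is no eSCCIP/eSCCIP-SP". On the intervention side, the resources listed are "intervention labor costs for hourly wages including fringe benefits of delivery staff for a different component of the program", specified as website maintenance staff and the telehealth guide. Other health care used by intervention families is not on that list. The section then says: "We will calculate net benefits, benefit-cost ratio, and return on investment", with bootstrap confidence intervals.

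Three other places bear on the point:

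- Study Outcomes, Table 1, schedules a service-use item at T1, T2 and T3, described as: "Questionnaire to measure contact and work with social work, psychology, psychiatry, pastoral care, community, and hospital-based services for all members of the family". The table also lists a chart review, with no time point marked.
- Limitations says: "We will also collect information on mental and psychosocial health services used by all participants during the study period". The purpose given is context and possible adjustment, not costing. The same paragraph says that "the use of these services is likely to be equivalent across intervention and control group participants", and that neither arm will be discouraged from using support.
- Randomization says: "Randomization will be conducted at the family level according to a 1:1 ratio between groups".

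**The concern.** A saving in service cost is a difference: what families would have used without the program, minus what they used with it. The randomized control arm is a sound source for the first term. The second term has to come from the intervention arm, and the Aim 3 text assigns it no record extraction, no unit costs and no place in the calculation. An analyst who follows the text as written holds record data for one arm and cannot form the between-arm difference from them.

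If the control-arm figure is then used as the saving, the error runs in one direction. It credits the program with removing all such use, including use that intervention families still had. The summary measures that set savings against costs would look better than the trial supports. The Abstract presents this aim as groundwork for future trials on dissemination and implementation, so these are the figures that later planning would draw on.

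**Working it through.** The documents give no figure for service use, unit cost or savings, so there is no plan figure to reproduce. The check is algebraic.

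**Inputs**
- C: mean related service cost per control family. Not given; set to 100 units as an assumption, for scale only.
- r: intervention-arm mean cost as a fraction of C. Not given; shown over a range.
- P: incremental program cost per family. Not given; kept as a symbol.
- Return on investment = net benefits / costs × 100 (Aim 3: Analyses).

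**Step 1: the saving**
- Between-arm saving = C - rC = C(1-r).
- Saving if control-arm use alone is taken = C.
- Overstatement = C - C(1-r) = rC. It is zero only when r = 0, that is, when intervention families use no such services.

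**Step 2: values with C = 100**

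| r | Between-arm saving | Control-arm use alone | Overstatement |
|---|---|---|---|
| 0 | 100 | 100 | 0 |
| 0.25 | 75 | 100 | 25 |
| 0.5 | 50 | 100 | 50 |
| 0.75 | 25 | 100 | 75 |
| 0.9 | 10 | 100 | 90 |
| 1.0 | 0 | 100 | 100 |
| 1.1 | -10 | 100 | 110 |

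The last row is a case in which contact with a guide leads families to use more services. Control-arm data alone would still show a saving of 100.

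**Step 3: downstream measures**
- Net benefit: C - P in place of C(1-r) - P, overstated by rC. The sign is wrong whenever P lies between C(1-r) and C.
- Benefit-cost ratio: C/P in place of C(1-r)/P, inflated by a factor of 1/(1-r). That is 2 at r = 0.5, 4 at r = 0.75 and 10 at r = 0.9.
- Return on investment: overstated by 100 × rC/P percentage points.

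**Step 4: does the bootstrap help?** Resampling control families describes the sampling error of C. The interval would be centered near C, not C(1-r), so the bias stays whatever the width of the interval.

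**Step 5: which r does the protocol suggest?** Limitations expects equal use of psychosocial support, which is r = 1 for those services. Aim 3 speaks of related health care use without defining it, so r = 1 is one documented scenario for the overlapping services and not an estimate for the whole cost.

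**The case against.** The strongest reply is that no savings formula is printed. The Aim 3 sentence can be read as naming only the source of the counterfactual term, with subtraction of intervention-arm use left unsaid. The section opens in incremental terms and promises best practice, which fits that reading. A journal article also commonly leaves the exact equation to a fuller document. This much stands: a reader might infer that the plan commits to crediting the full control-arm cost as saved, but the text does not say so.

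A reader might also infer that the protocol contradicts itself by expecting no difference in use while planning to report savings. The documents do not support that either. The Limitations statement concerns background psychosocial support, and the related health care use in Aim 3 is undefined and may be wider.

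The further reply, that intervention-arm data exist anyway, carries less weight. The chart review in Table 1 has no time point and no link to costs. The service-use questionnaire covers both arms, but it is self-report and is assigned to context and adjustment. Subtracting self-reported use in one arm from record-based use in the other would add measurement error that differs by arm. The plan names an arm for the record tracking, so this is a stated choice and not just an omitted detail.

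Finally, the cost work is exploratory, and the text calls it partial and preliminary. That limits the consequences. The limitation it admits, however, is incomplete information on program and implementation costs, not service tracking in one arm.

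**Conclusion.** The concern holds in a limited form. As written, the plan assigns record-based tracking for savings to the control group and says nothing of tracking, costing or subtracting intervention-arm use, so the stated record data cannot yield a between-arm saving. If control-arm use alone is taken as the saving, the overstatement is rC, from nothing at r = 0 to the whole of C at r = 1, and more than C if intervention families use more. That size is conditional on this use of the control-arm figure, and the value of r is unknown. The result touches net benefit, the benefit-cost ratio and return on investment in an exploratory evaluation. It does not touch the efficacy analysis or the sample size. It is worth correcting because the bias has one direction, the planned intervals would not reveal it, and the randomized comparison that removes it is already in the design.

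**What to change.** In Aim 3: Analyses, state that related service use will be extracted from the electronic record in the same way, for the same defined set of services and over the same window, in both randomized arms. Define savings as the control-minus-intervention difference in mean service cost across all randomized families, with the planned bootstrap confidence interval. Use that difference in net benefit, the benefit-cost ratio and return on investment. The questionnaire already scheduled at T1, T2 and T3 can serve as a check on the record data.

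The cost is a change of wording and record extraction for the intervention arm as well, planned at 175 families (350 split 1:1). The estimated saving will probably be smaller than control-arm use alone would suggest, and it could be zero or negative.

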### Data Quality

Data quality will be monitored throughout intervention implementation and data collection. The research team will routinely generate data quality reports (via built-in functionality) and meet biweekly to review the reports, discuss any identified issues (eg, missing data), and outline remedial actions. For the education control website, data from CopingSpace.org will be migrated to the same server that will host eSCCIP/eSCCIP-SP for ease of tracking and standardization. Once data collection is complete, a rigorous data cleaning, description, and covariate screening process will be carried out prior to analysis. Data will be first inspected for erroneous, outlying, or potentially high-leverage values, and missing data patterns tabulated and visualized. Data from the 3 recruiting study sites will then be pooled for analyses in 2 different versions of the data set separating participants who provide data for at least 1 measurement visit from participants who provide data at all time points. Multiple imputations will be used to handle missing data, including determination of a primary missing data mechanism, appropriate selection of auxiliary variables (if applicable), and sensitivity analyses to check for robustness of underlying assumptions (eg, MNAR selection models, pattern mixture models) [50]. Efficacy analyses will be carried out for both sets, thus providing a complete picture of whether and how missing data impact analysis results.

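### The cost analysis assigns sample selection and nonrandom attrition to a 2-part model, which addresses zero and skewed costs and cannot test or correct who is missing

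*Protocol article*

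**What the plan says.** The last sentence of Aim 3: Analyses in the Protocol article reads: "A 2-part model will be used to examine and handle sample selection and nonrandom attrition". It follows the cost regression: "Generalized linear models will be applied to estimate the relationship between program incremental costs and the characteristics of participants, providers, and programs", and then "Appropriate link function and distribution family will be chosen to fit the data". No selection equation, exclusion variable, weighting or imputation step is described for costs.

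The same section gives the sources of the cost data. For intervention costs, "we will document what was performed, by whom, the length of execution, and the use of any nonhuman resources". For cost savings, "we will use electronic patient record to track control group patients’ related health care service usage". The outputs include "marginal costs per unit of acute distress reduction", incremental cost-effectiveness ratios, net benefits and return on investment, with bootstrapping for uncertainty.

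Missing data in general are covered under Data Quality: "Multiple imputations will be used to handle missing data, including determination of a primary missing data mechanism", followed by MNAR sensitivity analyses of the selection-model and pattern-mixture type. That section ties its two versions of the data set to the efficacy analyses and does not name costs. The Limitations section states an intent-to-treat design and a comparison of completers with noncompleters.

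**The concern.** The plan rightly recognises nonrandom attrition as a threat to the cost analysis, but the remedy it names belongs to a different problem. A 2-part model describes costs among people whose costs are known. Its first part asks whether any cost was incurred, not whether the person was observed. A zero cost and a missing cost are different things, and the model speaks only to the first.

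The risk is that a reader takes the stated step as having dealt with attrition. The exposure is clearest in the cost-effectiveness ratios, because distress reduction is self-reported at follow-up, where 25% attrition is planned. Service use is also collected by questionnaire at all three time points in both arms, and the patient-record tracking is described only for the control group. Part of the resource-use information can therefore be lost with the caregiver.

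**Working it through.** **The plan's own figures.** The document gives no number for the cost analysis. The attrition rate is the input that matters here, and the sample size built on it reproduces. From Power Analyses and Sample Size Consideration: standardized difference 0.3, pretest-posttest correlation 0.5, power 80%, attrition 25%. From Aim 1: Analyses: two-sided 0.05.

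- Per arm: n = 2 × (1.960 + 0.842)² × (1 − 0.5²) / 0.3² = 2 × 7.85 × 0.75 / 0.09 ≈ 130.8, so 131.
- With attrition: 131 / 0.75 = 174.7, so 175 per arm and 350 in total, as stated.
- Expected with follow-up data: 350 × 0.75 = 262.5, so about 262 caregivers; about 88 would lack it.

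**What the 2-part model estimates.** For cost C and covariates x:

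E[C | x] = P(C > 0 | x) × E[C | C > 0, x]

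Both factors are fitted on records with C observed. Let R = 1 if the record is observed. The fit identifies P(C > 0 | x, R = 1) and E[C | C > 0, x, R = 1]. These equal the target quantities only if R is unrelated to C given x. The model assumes this condition and contains nothing that could test it.

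**Illustration.** All effect sizes below are assumptions, not figures from the protocol. There are 400,000 simulated records. A measured covariate x and an unmeasured factor u are independent standard normal.

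- Any cost occurs if 0.5 + 0.5x + 0.8u + logistic noise > 0.
- A positive cost equals exp(5 + 0.3x + 0.5u + 0.5 × normal noise).
- Dropout has logit a + g_x·x + g_u·u, with a set to give 25% dropout.
- The 2-part model (logistic, then gamma with log link, both on x) is fitted to observed records and standardised to everyone. The true mean cost is 141.2.

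| Dropout depends on | Error, plain mean of observed | Error, 2-part model |
|---|---|---|
| nothing (random) | 0.0% | 0.0% |
| modelled covariate, g_x = 1 | -9.7% | -0.3% |
| unmeasured factor, g_u = 0.5 | -8.6% | -8.7% |
| unmeasured factor, g_u = 1 | -16.6% | -16.6% |
| unmeasured factor, g_u = -1 | +13.2% | +13.2% |

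In the last three rows the 2-part model leaves the error where it was. In the second row the error disappears because x is in the model and the prediction is averaged over everyone; the 2-part structure is not what does that. The simulation concerns mean cost in a single group. It does not estimate bias in a between-arm ratio.

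**The case against.** The strongest reply is that little in the economic analysis hangs on this sentence. Several parts of that reply stand.

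- **Completers.** A reader might infer that cost estimates come from completers only and are therefore biased. The protocol does not say so. Staff and resource records and the electronic patient record need not stop when a caregiver stops answering questionnaires, and the stated principle is intent to treat.
- **Multiple imputation.** A reader might infer that the 2-part model replaces imputation for costs. The Data Quality section says in general terms "Multiple imputations will be used to handle missing data", and nothing in Aim 3 withdraws that. The distress outcome in the ratios is reasonably covered. What remains open is whether missing costs are covered too, since Aim 3 names another method for the same problem.
- **Headline measures.** A reader might infer that net benefit and return on investment would be reported as attrition-corrected. The 2-part sentence follows the cost regression and attaches most naturally to it. The text does not say that these measures are derived from that model.
- **Alternatives.** Imputation and weighting on observed variables also assume that dropout depends only on what is measured. They would not repair the last three rows of the table; only a sensitivity analysis for MNAR data addresses those.
- **Terminology.** The authors may have meant a two-step selection model. The article does not say so, and the two methods rest on different assumptions, so the sentence would still need correcting.

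None of this gives the 2-part model the property claimed for it. An article may leave detail to a fuller document, but this is a stated method paired with a purpose it cannot serve.

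**Conclusion.** The point holds in limited form. A 2-part model cannot examine or handle nonrandom attrition. Where dropout is related to cost or distress beyond the modelled covariates, cost regressions and cost-effectiveness ratios may stay biased after it is applied. The documents do not support the stronger statement that the cost estimates are biased.

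There is no bias under random dropout and next to none when modelled covariates explain dropout, and records-based costs may be largely unaffected. The simulated errors of -16.6% to +13.2% in mean cost show that the model leaves such bias in place under assumed effect sizes. They do not forecast this trial's error.

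Importance is low. The abstract calls the economic aim exploratory, Aim 3 describes it as a partial evaluation, and the primary efficacy result does not depend on it.

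**What to change.** 1. Keep the 2-part model, or the generalized linear model, for zero and skewed costs only, and remove the claim that it handles selection and attrition.
2. State that the multiple imputation under Data Quality also applies to missing cost and distress data in the economic analysis. Alternatively, use inverse-probability-of-retention weights based on site, language, baseline distress, the Psychosocial Assessment Tool score and T1 service use.
3. Run the imputation or weighting inside each bootstrap replicate, so that the intervals around the ratios, net benefits and return on investment reflect it.
4. Extend the MNAR sensitivity analyses already planned under Data Quality to the economic results, because step 2 alone does not correct dropout driven by unmeasured factors.
5. If a two-step selection model was intended, name it and give its selection equation.

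The cost is a change of wording and a little more programming. Site and language are the randomization strata, and the other predictors are collected at T1, so no new data are needed.
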